## Abstract

**Background:**

The metabolic syndrome is common across many complex chronic disease groups. Advances in health technology have provided opportunities to support lifestyle interventions.

**Objective:**

The purpose of this study is to test the feasibility of a health technology-assisted lifestyle intervention in a patient-led model of care.

**Methods:**

The study is a single-center, 26-week, randomized controlled trial. The setting is specialist kidney and liver disease clinics at a large Australian tertiary hospital. The participants will be adults with a complex chronic condition who are referred for dietetic assessment and display at least one feature of the metabolic syndrome. All participants will receive an individualized assessment and advice on diet quality from a dietitian, a wearable activity monitor, and standard care. Participants randomized to the intervention group will receive access to a suite of health technologies from which to choose, including common base components (text messages) and optional components (online and mobile app–based nutrition information, an online home exercise program, and group-based videoconferencing). Exposure to the optional aspects of the intervention will be patient-led, with participants choosing their preferred level of engagement. The primary outcome will be the feasibility of delivering the program, determined by safety, recruitment rate, retention, exposure uptake, and telehealth adherence. Secondary outcomes will be clinical effectiveness, patient-led goal attainment, treatment fidelity, exposure demand, and participant perceptions. Primary outcome data will be assessed descriptively and secondary outcomes will be assessed using an analysis of covariance. This study will provide evidence on the feasibility of the intervention in a tertiary setting for patients with complex chronic disease exhibiting features of the metabolic syndrome.

**Results:**

The study was funded in 2019. Enrollment has commenced and is expected to be completed by June 2022. Data collection and follow up are expected to be completed by December 2022. Results from the analyses based on primary outcomes are expected to be submitted for publication by June 2023.

**Conclusions:**

The study will test the implementation of a health technology–assisted lifestyle intervention in a tertiary outpatient setting for a diverse group of patients with complex chronic conditions. It is novel in that it embeds patient choice into intervention exposure and will inform health service decision-makers in regards to the feasibility of scale and spread of technology-assisted access to care for a broader reach of specialist services.

**Trial Registration:**

Australian New Zealand Clinical Trial Registry ACTRN12620001282976; https://www.anzctr.org.au/Trial/Registration/TrialReview.aspx?id=378337

**International Registered Report Identifier (IRRID):**

DERR1-10.2196/37556

## Introduction

The metabolic syndrome (MetS) is a combination of clinical risk factors, including central obesity, hypertension, dyslipidemia, and hyperglycemia [1]. Presence of the MetS is associated with increased risk of cardiometabolic complications, including cardiovascular disease and type 2 diabetes [2]. On a global scale, the MetS represents a substantial treatment burden due to increased costs and medication expenditure, hospitalization, and utilization of outpatient services [3,4]. The prevalence of the MetS is up to 60% in tertiary health care settings among patients with complex chronic conditions, including kidney and liver disease [5-7].

Specific components of the MetS may warrant pharmacotherapy, but this should only occur on a background of lifestyle intervention with a focus on diet quality and exercise [8-11]. Previous diet and exercise interventions in people with chronic disease have shown a cardioprotective effect [12-18]. However, the implementation of community-based diet and exercise management programs for complex chronic diseases has traditionally been challenging. Patients with chronic kidney or liver disease often have multimorbidity, potentially further compounding metabolic risk [19,20]. Management has traditionally required contact with multiple specialist teams across a siloed system, creating a significant burden for patients and caregivers [17,21]. Diet and exercise services have traditionally been delivered in condition-specific specialist settings, often with insufficient resources to deliver adequate services to address the health issues [22-24]. An integrated approach for the delivery of exercise and diet interventions through a unified complex chronic disease model of care could support improvement of cardiometabolic risk in tertiary care across specialist groups.

Advances in health technology have provided new opportunities to assist lifestyle interventions and improve the management of the MetS [13,17]. Asynchronous (eg, online information and resources) and synchronous (eg, telehealth appointments with health professionals) technology interventions have emerged as viable options for delivery of health care. These have the potential to address current barriers to service delivery, particularly in rural areas, including continuity of care, availability of resources, and location of services [25]. A range of factors within complex tertiary care systems, including patient-related factors (eg, values, goals, motivations, skills, and knowledge), organizational-related factors (eg, culture, priorities, and structural systems), and external factors (eg, health care funding), must be considered when assessing the feasibility of disruptive service change [26]. Patient-led approaches allow for the patient’s perspective to be considered when receiving health care [27]. These approaches ideally assist patients in individualizing their self-management plans through selecting which services they want to engage with and through what means.

This study will expand on the current literature by testing the implementation of a health technology–assisted lifestyle intervention for people with complex chronic disease. The primary aim will be to test the feasibility of this intervention, determined by safety, recruitment rate, retention, exposure uptake, and telehealth adherence. The secondary aims include assessing the clinical effectiveness of the intervention, (including metabolic syndrome severity, dietary quality, physical activity and sedentary behavior, exercise capacity, neuromuscular fitness, muscular pain, clinical parameters, quality of life, perceived confidence, fatigue, and sleep quality and quantity), patient-led goal attainment, treatment fidelity, exposure demand, and participant perceptions. We hypothesize that delivery of lifestyle interventions using health technology is feasible, can address the barriers to service delivery, and will demonstrate improved clinical outcomes over standard care.

## Methods

### Study Design and Setting

This is a single-center, 26-week, randomized controlled trial. The study is being conducted in a public hospital in a major metropolitan city in Queensland, Australia. The study design and flow are shown in Figure 1.

**Figure 1 figure1:**
[figure not shown]
Study design and participant flow, indicating the base components offered to all participants and the additional technology-assisted components offered to the intervention group.

### Participants and Eligibility Criteria

Adults living with kidney or liver disease who are at increased cardiometabolic risk and receiving specialist care at the Princess Alexandra Hospital in Brisbane, Australia, will be included. Eligibility criteria are shown in Textbox 1.

Eligibility criteria.
**Inclusion criteria**
Under the outpatient care of at least one of the following specialist Princess Alexandra Hospital clinics: kidney or liver transplant, chronic kidney disease, hemodialysis, peritoneal dialysis, or hepatologyHave (or be undergoing treatment for) at least one of the features of the metabolic syndrome, as defined by the harmonized criteria [1]:Elevated blood pressure (or on medication to treat) (systolic blood pressure ≥130 mm Hg and/or diastolic blood pressure ≥85 mm Hg)Elevated waist circumference (population- and country-specific definitions [1])Reduced high-density lipoprotein cholesterol (or on medication to treat) (<1.0 mmol/L in males; <1.3 mmol/L in females)Elevated fasting blood glucose (or on medication to treat) (≥5.6 mmol/L)Elevated triglycerides (or on medication to treat) (≥1.7 mmol/L)Deemed suitable to participate by treating medical specialistScreened as capable to participate by an exercise professionalHave current access to a mobile device or computer hardware with internet access and webcam capability
**Exclusion criteria**
Non–English speaking or unable to read and write in EnglishDocumented malnutritionUnder 18 or over 80 years of ageCurrently pregnant or breastfeedingLife expectancy less than 6 months

### Recruitment

The recruitment target will be 168 participants. Potentially eligible patients will be sourced via screening referrals to the dietetics department from a medical specialist. Referrals will be initially screened by the research project officer, and potentially eligible people will be contacted by phone to complete eligibility screening and be invited to participate. If a patient agrees to participate, a baseline appointment will be scheduled by the research project officer. Participant information and consent forms will be provided to patients via email prior to the baseline assessment, and written informed consent will be obtained at the baseline appointment. Age, sex, referring clinic, and inclusion and exclusion information for patients deemed ineligible or who decline to participate will be collected from electronic medical records. Ineligible patients will continue with the process of standard dietetic care as per usual practice guidelines. Demographic and medical data (Table 1) will be collected via online forms, review of medical charts, and phone calls prior to the baseline assessment. This is deemed a low-risk study, with expectations of behavior change no different from current usual care.

### Randomization and Allocation

Participants will be randomized 1:1 to the intervention group (group 1) or to a control group (group 2) that will receive standard care and individualized dietetic advice to support improvements in diet quality [28]. Computer-generated randomization will be completed using the REDCap research management system [29]. Groups will be stratified by referral source: (1) chronic kidney disease clinic, (2) hepatology clinic, or (3) liver or kidney posttransplant clinic. Participants will be informed of their group allocation following baseline assessment by the research project officer.

### Assessors and Blinding

Baseline assessments will occur prior to randomization. Assessors performing end-of-program clinical assessments will be blinded to group allocations. Assessor blinding will be verified by questionnaire at time of completion for each participant (Likert scale 1-5). This questionnaire will evaluate whether assessors have remained blinded to participant allocation. Participants will be reminded by the research project officer prior to end-of-program assessments to not disclose their group allocation to assessors.

### Quantitative Data Collection

Baseline demographic and medical history data that will be collected are listed in Table 1. Research outcomes and the associated measurement methods are outlined in Table 2. Primary outcomes will be assessed once all participants have finished the trial, and secondary outcomes will be collected at baseline and end-of-program assessments. Once a participant is randomized, the research staff will make every reasonable effort (eg, via phone calls, text messages, and emails) to follow the participant for the entire study period for collection of data.

**Table 1 table1:** Demographic and medical data collected prior to the baseline assessment.

Demographic and medical data	Measurements
Sex	Male or female
Date of birth	Date
Ethnicity	Caucasian, Indigenous, European, Anglo-Saxon, Asian, other, unknown/not reported
Marital status	Single or never married, living together, de facto or married, separated or divorced, widowed
Highest education level completed	Primary school, less than grade 10, grade 10, grade 12, vocational school or college, university
Employment status	Full-time, part-time, unemployed, self-employed, student, retired
Medication use	Listed medication intake including type, dose, and frequency
Menopause status	Yes, no, not applicable
Allergies	Yes, no, listed allergies
Cigarette smoking history	Former, current, never
Alcohol consumption	Number of standard drinks per week
Need for assistance to read written health materials^a^	Never, rarely, sometimes, often, always
eHealth literacy	eHealth Literacy Scale (eHEALS)^b^ questionnaire [30]

^a^Assessed through the following question via online form: “How often do you need to have someone help you when you read instructions, pamphlets, or other written material from your doctor or pharmacy?”

^b^eHEALS is a validated 8-question digital health literacy questionnaire that evaluates the ability to find the right type of health information online, where and how to find and use it, possession of the skills and confidence to evaluate the quality of online health information, and the perception of the usefulness and importance of accessing online information for health [30]. This will be administered via an online form.

**Table 2 table2:** Primary and secondary outcomes and their associated measurements.

Outcomes					Measurements
**Primary outcomes**					
	Safety			Number of study-related serious adverse events	
	Recruitment rate			Number of patients recruited as a proportion of all referred eligible patients	
	Retention			Number of intervention participants undergoing end-of-program assessment	
	Exposure uptake			Frequency of dietetic and exercise specialist contact (within public hospital system) as a proportion of total scheduled contacts	
	Telehealth adherence			Attendance to online exercise and dietetic sessions as a proportion of total scheduled contacts	
**Secondary outcomes**					
	**Clinical effectiveness**				
		Metabolic Syndrome Severity Score [31]	Algorithm score comprising systolic blood pressure, diastolic blood pressure, waist circumference, triglycerides, high-density lipoprotein cholesterol, and fasting blood glucose		
		Dietary quality	Diet quality assessed by food group intake (frequency per day or week), fiber intake (grams per day), unsaturated oils (grams per day), and discretionary food intake (grams per day)		
		Physical activity and sedentary behavior	Time (intensity-weighted minutes) spent in past week as assessed by International Physical Activity Questionnaire (Short Form) and Fitbit weekly physical activity heart rate data		
		Exercise capacity	6-Minute Walk Test score		
		Neuromuscular fitness	Single chair stand, Five Times Sit to Stand test, hand grip strength		
		Muscular pain	Modified Nordic Musculoskeletal Questionnaire		
		Quality of life	European Quality of Life Five Dimension Five Level Scale		
		Nutrition and physical activity management self-efficacy	Likert confidence scales		
		Fatigue	Functional Assessment of Chronic Illness Fatigue Scale score		
		Sleep quality and quantity	Pittsburgh Sleep Quality Index score, total Fitbit weekly sleep data		
		Additional clinical parameters	Resting heart rate, BMI, serum biochemical analytes (Multimedia Appendix 1)		
	Goal attainment			Goal Attainment Scale score	
	Treatment fidelity			Treatment notes^a^ Staff attendance at professional support and case discussions	
	Exposure demand			Selection of health technology options	
	Participant perceptions			Feedback survey Qualitative individual interview data (subsample)	

^a^Participant session notes taken by health professionals from telehealth-facilitated sessions with the intervention group.

### Primary Outcome

The primary outcome is feasibility (Table 2), which will be used to inform future service delivery. Feasibility success will be confirmed if the intervention is safe (defined as a similar number of study-related serious adverse events [SAEs] between groups) and if three of the following four criteria are fulfilled: (1) ≥50% of all referred eligible patients are recruited (recruitment), (2) ≥70% of intervention participants undergo an end-of-program assessment (retention), (3) ≥75% of intervention participants have a higher frequency of specialist outpatient dietetic and exercise specialist contact than the controls (exposure uptake), and (4) videoconferencing-facilitated dietetic and exercise sessions have an attendance rate of ≥80% of the total scheduled contacts (telehealth adherence).

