### All Participants

All participants will receive usual medical and specialist care and may choose to discontinue contact with the health professionals at any time during the study period. All participants will be offered an individualized in-person appointment with a dietitian, review appointments, and a wearable activity monitor. Patients do not currently have access to exercise physiology services as part of standard care.

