### Intervention

Participants randomized to the intervention group will be offered access to a suite of health technology options with both core (text message support) and optional (electronic dietary education resources, group-based exercise physiology and dietetics videoconferencing appointments, and an unsupervised online or mobile app home exercise program) components. Exposure to the frequency of text messages and the number and type of optional components will be patient-led, with participants choosing their preferred level of engagement (Figure 1). Participants will choose their components after randomization and the research project officer will confirm their choice via phone call in week 1. The core and optional components are described in the following sections.

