#### Primary Analysis

The primary analysis will evaluate the feasibility of the intervention. As mentioned previously, the feasibility of the intervention will be determined by evaluating safety and if three of the following four criteria are achieved: (1) recruitment rate ≥50%, (2) retention ≥70%, (3) exposure uptake ≥75%, and (4) telehealth adherence ≥80%. Safety will be assessed by comparing the number of study-related SAEs in the intervention and control groups using a chi-square test of homogeneity. The safety of the intervention will be assumed if there are no statistical differences between the groups.

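### Exposure uptake, one of four primary feasibility criteria, has two incompatible definitions that can give opposite verdicts

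*Protocol article*

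**What the plan says.** Feasibility requires acceptable safety and is confirmed "if three of the following four criteria are fulfilled". The third criterion, in the Primary Outcome section, is "≥75% of intervention participants have a higher frequency of specialist outpatient dietetic and exercise specialist contact than the controls (exposure uptake". That section also cites Table 2 for the outcome, and the Quantitative Data Collection section names Table 2 as the place where measurement methods are set out. Table 2 gives exposure uptake as "Frequency of dietetic and exercise specialist contact (within public hospital system) as a proportion of total scheduled contacts". The Primary Analysis section refers back to the earlier statement and lists only "3) exposure uptake ≥75" per cent.

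Three other statements bear on the point:

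- Telehealth adherence, the fourth criterion, is in Table 2 "Attendance to online exercise and dietetic sessions as a proportion of total scheduled contacts".
- On the control side, the All Participants section says "Patients do not currently have access to exercise physiology services as part of standard care". Both arms are offered a dietitian appointment and reviews.
- In the intervention arm, "the number and type of optional components will be patient-led". Dietetic video sessions are monthly and exercise video sessions weekly. Option 4 has no exercise video sessions, but an exercise physiologist updates the home programme each month.

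**The concern.** The two statements differ in unit (contact or participant), in denominator (scheduled contacts or intervention participants) and in comparator (none or the controls). An analyst can follow either and point to the protocol. The result feeds a go/no-go rule, so a definition settled after the data are seen could change the trial's main conclusion.

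Each version also has a weakness of its own. The Table 2 version sits close to telehealth adherence, so two of the four criteria would tend to move together. The Primary Outcome version depends heavily on which options patients pick, because controls have no exercise physiology service to match. Option choice is already a separate secondary outcome (Exposure Demand).

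**Working it through.** **The plan's own figure.** The feasibility criteria have no calculation. The only one is the sample size for the metabolic syndrome severity score: 2 × (1.96 + 0.8416)² × 1.9² × (1 − 0.5²) / 0.8² = 66.4, so 67 per arm. Then 67 / 0.80 = 83.75, so 84 per arm and 168 in total. This reproduces. It is used here only for the arm size; 75% of 84 is 63 participants.

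**The two definitions.**

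| | Table 2 (A) | Primary Outcome (B) |
|---|---|---|
| Unit | contact | participant |
| Denominator | scheduled contacts | intervention participants |
| Comparator | none | the controls, statistic not named |
| Threshold stated there | none | 75% |

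**Can the verdicts differ?** Inputs from the protocol: 84 per arm, and over 26 weeks 26 weekly exercise and about 6 monthly dietetic video sessions. Inputs assumed, because the protocol gives no figure: in both arms 1 + Poisson(3) scheduled individual dietetic contacts, each kept with probability 0.9; independent choice of the two video options; a common attendance probability; Option 4 updates not counted; A calculated in the intervention arm; the 75% threshold applied to either definition. There were 2000 simulated trials per setting.

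*Many choosers, moderate attendance* (80% choose exercise video, 50% dietetic video, 50% attendance). Expected contacts per participant:
- scheduled: 4 + 26 × 0.8 + 6 × 0.5 = 27.8
- kept: 3.6 + 0.5 × 23.8 = 15.5
- A = 15.5 / 27.8 = 56%, a fail
- B against the control median (simulated) = 93%, a pass

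*Few choosers, high attendance* (30%, 20%, 90%):
- scheduled: 4 + 26 × 0.3 + 6 × 0.2 = 13
- kept: 3.6 + 0.9 × 9 = 11.7
- A = 11.7 / 13 = 90%, a pass
- B (simulated) = 67%, a fail on average, passing in 16% of runs

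**Effect on the overall rule.** In the first setting telehealth adherence is 50% and fails. If recruitment and retention both pass, A gives two of four (not feasible) and B gives three (feasible). In the second setting telehealth adherence is 90% and passes. If exactly one of recruitment and retention passes, A gives three of four and B gives two.

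**Comparator statistic within B.** With 70% and 50% choosing and 50% attendance, B is 0.90 against the control median, 0.92 against the mean and 0.72 against the maximum. The last fails.

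**What drives B.** With the choice pattern fixed, raising attendance from 30% to 90% moves B against the median by 1 to 4 points. Raising the share choosing exercise video from 30% to 90% (dietetic video from 20% to 60%) moves it from 0.63–0.67 to 0.96–0.98.

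**Overlap of A with telehealth adherence.** Across the choice patterns tried, A was 0.64–0.69 at 60% video attendance and 0.90 at 90%, so it largely follows the attendance rate.

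**The case against.** The best defence is that the Primary Analysis section refers back to the Primary Outcome section, the only place where 75% has a meaning. Table 2 sets no thresholds and is loosely worded elsewhere: retention is a number there but a percentage in the criterion. An analyst following the decision rule would probably use the participant-level version. That lean is real. It does not settle the matter, because the Primary Outcome section itself cites Table 2, and Table 2 is named as the source of the measurement methods.

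One could try to merge the two by comparing each participant's attended-to-scheduled ratio with the controls' ratio. The criterion speaks of a higher frequency, not a higher proportion, and this reading gives a third answer (0.03 to 0.61 in the same simulation).

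The choice of mean or median could fairly be left to an analysis plan. Alone it would not be a finding; here it adds to a conflict the protocol states outright.

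It is also fair to say that more specialist contact than controls is a sensible thing to test, since the Discussion expects improved access, and that patients declining contact is itself a feasibility result. This stands. The dependence on choice is something to make visible, not an error in itself.

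**Conclusion.** The conflict between Table 2 and the Primary Outcome section is in the text and needs no assumption. Its possible size does: 56% against 93%, and 90% against 67%, rest on the assumed contact and attendance rates and on applying 75% to either definition. The definition decides overall feasibility only when exactly two of the other three criteria are met. That B follows option choice more than attendance is an inference from the patterns tried. Against the control maximum, attendance matters more, by up to about 17 points.

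Two stronger readings are not supported:

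- A reader might infer that B must fail once more than a quarter of patients choose no video sessions, so that 70% choosing caps the result at 70%. That needs every non-chooser to tie with or fall below the comparator. Both arms are offered dietitian reviews, so counts will vary. With share f choosing and attending enough to exceed the control median, and non-choosers distributed like controls, B = f + (1 − f)q. For Poisson means 1 to 4, q = 0.264 to 0.371, so f = 0.70 gives 0.70 + 0.30 × 0.264 = 78% to 0.70 + 0.30 × 0.371 = 81%, a pass. Break-even is f of about 60% to 66%.
- A reader might infer that Table 2 uptake and telehealth adherence are the same measure. Uptake covers all such contact within the public hospital system, including in-person dietitian visits; adherence covers online sessions only. They overlap substantially but are not identical.

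**What to change.** Before analysis, put one definition in Table 2, the Primary Outcome section and the Primary Analysis section: the percentage of all randomised intervention participants whose number of attended dietetic plus exercise specialist contacts over 26 weeks is strictly greater than the control-arm median, with ties not counted. Remove the scheduled-contacts denominator from the uptake row of Table 2. State whether the monthly Option 4 updates by the exercise physiologist count as contacts.

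As descriptive support, report dietetic and exercise contacts separately, and give the result among those who chose a videoconferencing option. This does not remove the dependence on choice, but it shows how far a pass reflects the absence of an exercise service for controls.

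The cost is a wording amendment and two extra descriptive summaries, with no new data.
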